## Abstract

**Background:**

Beneficial and detrimental effects of various vegetarian and vegan diets on the health status are well known. Considering the growing background numbers of vegetarians and vegans, the number of vegetarian and vegan runners is likely to rise, too. Therefore, the Nutrition and Running High Mileage (NURMI) Study was designed as a comparative study to investigate the prevalence of omnivores, vegetarians, and vegans in running events and to detect potential differences in running performance comparing these three subgroups.

**Methods/design:**

The NURMI Study will be conducted in three steps following a cross-sectional design. Step 1 will determine epidemiological aspects of endurance runners (any distance) using a short standardized questionnaire. Step 2 will investigate dietary habits and running history from eligible participants (capable of running a half-marathon at least) using an extended standardized questionnaire. Step 3 will collect data after a running event on finishing time and final ranking as well as a post-race rating of perceived exertion, mood status, nutrient and fluid intake during the race.

**Discussion:**

Our study will provide a major contribution to overcome the lack of data on the prevalence and running performance of vegetarian and vegan runners in endurance running events. We estimate the prevalence of vegetarians and vegans participating in a running event to be less compared to the respective proportion of vegetarians and vegans to the general population. Furthermore we will validate the subject’s self-assessment of their respective diet. This comparative study may identify possible effects of dietary behavior on running performance und may detect possible differences between the respective subgroups: omnivorous, vegetarian and vegan runners.

*Trial registration* Current controlled trials, ISRCTN73074080

## Background

The Academy of Nutrition and Dietetics (formerly the American Dietetic Association) publishes position papers to vegetarian diets since 1980. The position paper of 2009 states that well-planned vegetarian diets, including total vegetarian or vegan diets, are appropriate for individuals during all stages of the lifecycle, including pregnancy, lactation, infancy, childhood, and adolescence, and for athletes (Craig and Mangels 2009).

The current position paper states that well-designed vegetarian diets, that may include fortified foods or supplements, meet current nutrient recommendations and are appropriate for all stages of the life cycle, including pregnancy, lactation, infancy, childhood, and adolescence (Cullum-Dugan and Pawlak 2015).

Numerous reputable studies (e.g. EPIC Oxford, Adventist health Study 1&2, and GEICO Study) described distinct advantages of vegetarian or vegan diets compared to diets containing meat and other foods of animal origin (Appleby et al. 1999; Davey et al. 2003; Le and Sabaté 2014; Mishra et al. 2013; Tonstad et al. 2013).

Health related benefits of vegetarian diets range from lower mortality from all-causes (Li 2014; Orlich et al. 2013) to lower body weight (BW), Body-Mass-Index (BMI) (Williams 1997), blood pressure (Yang et al. 2011), risk of obesity, and incidence of type 2 diabetes (Chiu et al. 2014; Zhang et al. 2010), as well as an enhanced antioxidant status capable of reducing exercise-induced oxidative stress (Kim et al. 2012; Trapp et al. 2010). Generally, the health of vegetarians is sound and compares favorably with that of the non-vegetarians (Appleby et al. 1999; Deriemaeker et al. 2011). As for all kinds of nutrition schemes, the health of vegans depends on their knowledge of how to compose and appropriately supplement their diet (Gilsing et al. 2010; Key et al. 2006; Le and Sabaté 2014; Obersby et al. 2013).

Since vegetarians consume widely divergent diets, a differentiation between various types of vegetarian diets is necessary. Many misunderstandings concerning vegetarianism are due to scientific data from studies without this differentiation. In the past, vegetarian or vegan diets have been described as being deficient in several nutrients including vitamin B_12_ (Gilsing et al. 2010; Obersby et al. 2013) iron, zinc, calcium, omega-3 fatty acids and iodine (Key et al. 2006). Numerous studies have demonstrated that the observed deficiencies are usually due to poor meal planning (Leitzmann 2005).

Although there has been some concern about protein intake for vegetarian and vegan athletes, data indicate that all essential and non-essential amino acids can be supplied by plant food sources alone as long as a variety of foods are consumed and the energy intake is adequate (Nieman 1999). Furthermore well planned, varied, appropriately supplemented vegetarian and vegan diets high in nutrient density appear to successfully and effectively support parameters that influence athletic performance (Rodriguez et al. 2009), nutritional requirements, recovery and resistance to illness in athletes (Barr and Rideout 2004; Eisinger et al. 1994; Fuhrman and Ferreri 2010). Yet, some athletes, regardless of diet, may lack nutritional knowledge critical to preventing nutrition-related health problems. However, most athletes have positive attitudes toward nutrition and are receptive to nutritional counseling (Zawila et al. 2003).

Considering the growing background numbers of vegetarians and vegans (Stahler 2011; Vegetarierbund Deutschland 2015), we assume that the number counts of vegetarian and vegan runners is rising, too. Among Europeans, 5 % of the population are estimated vegetarian or vegan adding up to 37 million vegetarians and vegans overall (European Vegetarian Union 2015). Considering German speaking European countries (Austria, Germany, and Switzerland), 9 % of the Austrian population or 760,000 are estimated vegetarian and 80,000 vegan (Hnat 2015). In Germany 10 % of the population or 7.8 million are estimated vegetarian and 1.1 % or 900,000 vegan (Vegetarierbund Deutschland 2015). 5 % of the Swiss population is estimated vegetarian (Schweizerische Vereinigung für Vegetarismus 2015).

There are many vegetarian and vegan athletes especially in endurance and ultra-endurance disciplines such as Alan Murray and Janette Murray-Wakelin (marathon running) (Murray and Murray-Wakelin 2015), Michael Arnstein (marathon running) (Arnstein 2015), Fiona Oakes (marathon running), Vlad Ixel (ultra-marathon running), Scott Jurek (ultra-marathon running), Ruth Heidrich (triathlon) (Greatveganathletes.com 2015), Emil Voigt (Olympic track and field), Edwin Moses (Olympic track and field), Paavo Nurmi (Olympic track and field) (Finn 2015), Brendan Brazier (triathlon) (Braizer 2015), and Arnold Wiegand (ultra-triathlon) (Wiegand 2015).

Considering these and numerous other successful (ultra-) endurance athletes adhering to various vegetarian and vegan diets provides sufficient evidence that high-level endurance and ultra-endurance performance can be achieved by following a vegetarian or vegan diet. Therefore it is reasonable to conclude that a vegetarian or vegan diet is compatible with successful endurance and ultra-endurance performance. Yet the prevalence of vegetarians or vegans in endurance running events has not been investigated to date.

Scientific data about endurance and ultra-endurance athletes following a vegan diet is limited. Only two case reports describing vegan diet and athletic performance can actually be found in PubMed database (MEDLINE Database 2015). Wirnitzer and Kornexl (2014) described the successful implementation of a vegan diet during an 8-day mountain bike race of a female athlete. Leischik and Spelsberg (2014) investigated an ultra-endurance triathlete on a raw vegan diet, with reference to his ability to perform, cardiac status, and any symptoms of deficiency.

Since case reports are not adequate to draw any scientific conclusions to a larger population, the NURMI Study was designed as a comparative study with a large study population to investigate the prevalence in running events and to detect potential differences in running performance comparing three subgroups: omnivorous, vegetarian and vegan endurance runners.

The future results of the NURMI Study might be useful to develop adequate strategies on nutrition behavior and might help to design individualized interventions in order to meet the nutritional challenges of demanding endurance running races and the requirements of vegetarian and vegan endurance runners.

### Trial objectives

The first and major goal of the NURMI Study is to compare endurance performance of vegetarian and vegan runners to non-vegetarian marathon runners and to determine potential differences/to identify possible correlations.The second goal is to investigate the prevalence of vegetarian and vegan runners in endurance (half-marathon and marathon) events.The third goal is to validate the subjects self-reports on his/her dietary behavior.

## Methods

The NURMI Study was designed by an interdisciplinary team of primary care physicians, sports medicine specialists, sport scientists, and nutrition scientists. An overview of all components of the intervention is shown in Fig. 1.

**Fig. 1 Fig1:**
[figure not shown]
Timescale of the NURMI Study

### Step 1

Epidemiological pre-study

Step 1 is composed of a short standardized online questionnaire for endurance and ultra-endurance runners (any distance and any level of performance) primarily in Austria, Germany and Switzerland. Data on sex, age, kind of diet, and running history and habits will be collected. We aim to approach as many runners as possible for this step since gathered data will be used to estimate the prevalence of vegetarians and vegans active in endurance running.

### Step 2

The major NURMI Study questionnaire

Runners matching inclusion criteria of the respective subgroups (capable of running a half-marathon etc./see “Subjects” section) complete an extended questionnaire on health status, specific dietary habits (details of consumption of specific foods or food groups), running history (i.e. preferred running distance, finished races overall and number of completed races in the last 2 years, preparation for a specific event, average distance and training load per day/week, etc.) and exercise induced diet (i.e. during training, racing or a day of rest, nutritional strategy on race day, etc.) as well as quality of life and health-related behavior. Step 2 includes a short form of the Quality of Life questionnaire (QOL BREF 26) distributed by the World Health Organization.

### Step 3

NURMI post-race testing

After individual finishing a race of at least half-marathon distance, runners complete a questionnaire on final ranking, finishing time, energy and fluid intake, in race dietary strategy, and physical and mental perception. The rate of perceived exertion (RPE, overall, leg muscles and respiratory system) will be assessed by using the Borg Scale (Borg 1998).

### Subjects

A large number of runners is planned to be enrolled in order to reach a sufficient number of subjects especially for Step 1. For Step 2 and 3 runners will need to meet the inclusion criteria. Runners participating in the NURMI Study will be recruited via advertisement by various channels such as directly at the websites of the organizers of marathon events, online running communities, and specific mailing-lists for runners, runners’ magazines as well as magazines for health, vegetarian nutrition and lifestyle and personal communication. Additionally, information will also be provided by the official website (www.nurmi-study.com). Core region are German-speaking countries of Europe (Germany, Austria, Switzerland).

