#### Inclusion criteria

For the epidemiological pre-study (Step 1) any subject active in running (any distance as well as any performance level) can participate. For successful participation in the main study (Step 2 and 3) a complete data set consisting of the following four items is required: written informed consent (1), at least 18 years of age (2), all NURMI questionnaires completed (3), successful participation in a running event of either half-marathon or marathon distance (4).

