### Outcomes

#### Primary outcomes

In addition to running performance (individual marathon finishing time of Step 3) adjusted to performance level the primary outcome is the prevalence of kinds of diets (omnivorous, vegetarian, vegan) among runners attending running events.

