### Limitations of the study

Not all vegetarians and vegans participating in running events may be within the reach of the various recruitment methods. Due to various season, daytime and location of races, environment conditions (e.g. weather including sun or rain, temperature, relative humidity) will vary among the respective running events. Furthermore, our study shares with others the limitation of the cross-sectional design; therefore the present investigation allows no conclusion regarding causality. Prospective cohort studies are needed to confirm the associations between specific kinds of diet, health status and endurance performance to assess the causal direction and to develop recommendations for nutritional intake for vegetarian and vegan runners for training and racing.

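### The primary diet-prevalence outcome rests on an opt-in survey advertised partly in vegetarian media, so the vegetarian and vegan share is probably biased upward by an amount that sample size cannot reduce

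*Protocol article*

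**What the plan says.** All references are to the protocol article.

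- **Outcome.** Primary outcomes states, alongside running performance, that "the primary outcome is the prevalence of kinds of diets (omnivorous, vegetarian, vegan) among runners attending running events".
- **Target population.** The second goal under Trial objectives is "to investigate the prevalence of vegetarian and vegan runners in endurance (half-marathon and marathon) events".
- **Data source.** Step 1 is a short online questionnaire, and its "gathered data will be used to estimate the prevalence of vegetarians and vegans active in endurance running". The section aims to reach as many runners as possible.
- **Eligibility.** For Step 1, "any subject active in running (any distance as well as any performance level) can participate" (Inclusion criteria).
- **Recruitment.** Subjects gives one list of channels for the whole study. It names event organisers' websites, running communities, runners' mailing lists and runners' magazines, and also "magazines for health, vegetarian nutrition and lifestyle and personal communication".
- **Expectation.** The Discussion part of the abstract says: "We estimate the prevalence of vegetarians and vegans participating in a running event to be less compared to the respective proportion" of vegetarians and vegans in the general population. Background gives vegetarian shares of 10 % for Germany (with 1.1 % vegan), 9 % for Austria and 5 % for Switzerland.
- **Acknowledged limitation.** On recruitment, Limitations of the study says only: "Not all vegetarians and vegans participating in running events may be within the reach of the various recruitment methods".

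**The concern.** A prevalence estimate needs the chance of entering the sample to be unrelated to diet, or related to it in a known way. Here people choose to answer a survey for a study with nutrition in its name, and one advertising channel is defined by diet. The vegetarian share among respondents then reflects advertising reach and interest in the topic as well as prevalence. Recruiting extra vegetarians and vegans helps the diet comparison in Steps 2 and 3, but the same channels feed Step 1, where it does harm.

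At stake is the reading of a primary outcome. The authors expect a prevalence below that of the population, and differential response alone could push the observed figure above it. Collecting more responses narrows the interval around the wrong value. The one recruitment limitation acknowledged is under-coverage of vegetarians and vegans, which points away from the likelier error.

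A second, separate problem is that the eligible population (anyone who runs) is not the target population (half-marathon and marathon participants).

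**Working it through.** **The plan's own figures.** No sample size or precision is stated for prevalence. The only sizes given, 179 men and 159 women, concern weight loss during a race. They reproduce with the one-sample formula n = (SD × (1.960 + 0.842) / difference)²:

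- men: (8.1 × 2.802 / 1.7)² ≈ 178.2, rounded up to 179
- women: (6.3 × 2.802 / 1.4)² ≈ 158.9, rounded up to 159

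They have no bearing on prevalence.

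**Inputs.** The comparators come from Background: 10 %, 9 % and 5 %. The true share p among runners and the relative response k (vegetarians and vegans against omnivores) are not in the document. Both are assumed here and shown as ranges.

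**Expected observed share:** q = kp / (kp + 1 − p)

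| True p | k = 1.5 | k = 2 | k = 3 | k = 5 |
|---|---|---|---|---|
| 5 % | 7.3 % | 9.5 % | 13.6 % | 20.8 % |
| 8 % | 11.5 % | 14.8 % | 20.7 % | 30.3 % |

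**Response ratio at which the expected result disappears:** k* = [P / (1 − P)] / [p / (1 − p)], with P the population figure.

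- P = 10 %, p = 5 %: (0.10/0.90) / (0.05/0.95) = 2.11
- P = 10 %, p = 8 %: (0.10/0.90) / (0.08/0.92) = 1.28
- P = 9 %: 1.88 at p = 5 % and 1.14 at p = 8 %
- P = 5 %, p = 3 %: 1.70

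The text does not say whether the German 1.1 % vegans are included in the 10 % vegetarians. If they are additional, P = 11.1 %, and k* becomes (0.111/0.889) / (0.05/0.95) = 2.37 at p = 5 % and 1.44 at p = 8 %.

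**Bias against random error.** At p = 8 % and k = 2 the bias is 14.8 − 8.0 = 6.8 percentage points at any n. The 95 % half-width at a share of 10 %, 1.96 × √(0.10 × 0.90 / n), is 1.9 points at n = 1000 and 0.8 points at n = 5000.

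**Effect on a comparison with 10 %** (p = 8 %, assumed n = 2000, two-sided 5 % level, normal approximation). The chance of a result significantly below 10 % is 87 % at k = 1 and about 0 % at k = 2. At k = 2 a significantly higher result is almost certain.

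**If the bias ran the other way.** At k = 0.5 a true 10 % would appear as 5.3 %. The direction therefore matters to how any result is read.

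**Target population.** Set side by side, Trial objectives asks about half-marathon and marathon events, and Inclusion criteria opens Step 1 to any distance. Secondary outcomes lists, for Step 1, races attended in the past 2 years and distances finished. The mismatch can therefore be largely reduced at analysis; self-selection cannot.

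**The case against.** Four counter-arguments deserve weight.

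1. **Direction and size.** A reader might infer that the estimate is inflated as a matter of fact. The document does not establish that. Most of the listed channels are running channels, the vegetarian magazines are one item among several, and nothing shows how many respondents each supplies. Upward bias is likely; its size is unknown. The values of k and p above are illustrations only.

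2. **Whether the expectation can be examined.** A reader might infer that Step 1 cannot test the expectation at all. That is too strong. If the bias is upward, an observed share below the population figure supports the expectation all the more; only an equal or higher share is uninterpretable. The expectation is also a single sentence in the abstract, and Statistical methods specifies no test against population figures.

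3. **Any-distance eligibility.** A reader might infer that open eligibility itself raises the vegetarian share. Nothing in the document supports that. It is a separate question of target population, and the items needed to select event runners are already collected.

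4. **Priority and remedy.** Performance is called the first and major goal and prevalence the second. Channel tracking cannot remove interest in the topic, and Step 1 has been open since October 2014, so earlier respondents may have no channel on record. Whether a referral source is already captured cannot be known from a condensed article.

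All four narrow the claim. They do not remove it: Primary outcomes does name prevalence as primary, the channels and the open eligibility are stated rather than missing, and the limitation given covers only under-coverage.

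**Conclusion.** The concern holds in a limited form. A primary outcome is to be estimated from a sample whose selection depends in part on that outcome. The vegetarian and vegan share is probably biased upward, by an amount that the document does not allow to be derived and that a larger sample will not reduce. Under assumed true shares of 5 % and 8 %, response ratios of about 2.1 and 1.3 would erase the expected shortfall against the German 10 % (about 2.4 and 1.4 if vegans are counted in addition). These are modest ratios for a diet-themed survey advertised partly to vegetarians, but that judgement is not a figure from the document.

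The outcome is therefore readable in one direction only, and only if the bias is indeed upward: a share below the population figure would support the expectation, and one at or above it could not be interpreted. The gap between any-distance eligibility and the half-marathon and marathon objective is a second, separable point that data already collected can largely address.

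**What to change.** 1. **Restrict the prevalence analysis** to Step 1 respondents who report a half-marathon or marathon in the past 2 years, using the items on races attended and distances finished. If the two items are not linked, require any race in the past 2 years together with a finished half-marathon or marathon, and say so.
2. **Record the recruitment channel** from now on, by one question or separate links, while the questionnaires remain open (through 31 December 2015). Exclude respondents from vegetarian media from the prevalence estimate, and report each proportion with a 95 % confidence interval by channel. Those excluded can stay in the Step 2 and 3 comparison.
3. **Word the result modestly.** Interest in the topic remains in every channel, and earlier respondents may have no channel recorded. Describe the result as the diet distribution of the sample, and drop the comparison with the general population or qualify it explicitly.
4. **Extend Limitations of the study** to name likely over-recruitment of vegetarians and vegans, beside the under-coverage already mentioned.

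The cost is one questionnaire item or tracked link and some rewording. The prevalence sample becomes smaller, its interval wider and the claim more modest. These steps reduce the self-selection but do not remove it.

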#### Inclusion criteria

For the epidemiological pre-study (Step 1) any subject active in running (any distance as well as any performance level) can participate. For successful participation in the main study (Step 2 and 3) a complete data set consisting of the following four items is required: written informed consent (1), at least 18 years of age (2), all NURMI questionnaires completed (3), successful participation in a running event of either half-marathon or marathon distance (4).

### Description of measurements/methods/data collection

#### Questionnaires

All questionnaires are standardized, based on self-report, and will be conducted as online-surveys. Subjects can access www.nurmi-study.com and complete all questionnaires via encrypted interface.

#### Further measurements

Individual finishing time will be measured by the running events professional timing system and will be calculated as percentage of the overall winner’s time.

#### Voluntary physical examination (optional)

Study participation does not involve any specific invasive type of intervention. Yet, we strongly advise the subjects to undergo a medical checkup including both a blood test and an incremental exercise test on a treadmill prior to the running event. Both can be conducted by a physician and analysed at a professional diagnostics laboratory at the runners hometown to determine critical micronutrient levels of iron, haemoglobin, serum ferritin, haematocrit, magnesium, serum vitamin B_12_, holo transcobalamin, homocysteine and zinc, as well as to determine laboratory running performance. Participants will need to pay full cost for this voluntary laboratory testing, since it is optional. Subjects will be asked to measure body weight before and after the running event chosen for Step 3.

